## Abstract

**Background:**

Vaccine effectiveness is usually determined in randomized controlled trials (RCT) and if effective, additional information, e.g. on cost-effectiveness, is required to allow evidence-based decision making. A prerequisite for proper health economic modelling is the availability of good quality data on health care resources use, health outcomes and quality-of-life (QoL) data. The “Collecting health outcomes and economic data on hospitalized Community Acquired Pneumonia (CHO-CAP) – a prospective cohort study” is executed alongside the Community Acquired Pneumonia Immunization Trial with Adults (CAPiTA trial) to capture health outcomes and economic data of elderly hospitalized with CAP and matched controls without CAP.

**Methods/Design:**

CAPiTA is a placebo-controlled double-blind RCT evaluating the effectiveness of a 13-valent conjugated pneumococcal vaccine in preventing vaccine-type pneumococcal CAP in 84,496 elderly in the Netherlands. Participants of CAPiTA, who consented and provided information on health status (EQ-5D) and socio-demographic background at the time of vaccination, constitute the source population of CHO-CAP and are eligible for the nested matched cohort study. CHO-CAP patients hospitalized with CAP form the “diseased” cohort and the “non-diseased” cohort consists of unaffected persons (i.e. no CAP). Observations in the diseased cohort and in matched controls from the non-diseased cohort are used to determine excess costs and QoL changes attributable to CAP.

Based on an estimated 2,000 CAPiTA participants being hospitalized with CAP and an assumed CHO-CAP participation rate of 30% of all CAPiTA participants (±25,000), 600 CAP episodes are expected among CHO-CAP participants (the “diseased” cohort). For each patient with CAP, two non-diseased CHO-CAP subjects will be selected from the CHO-CAP cohort, with matching for age, gender and EQ-5D baseline-score. Data on healthcare and non-healthcare resources use, quality-of-life (using EQ-5D and SF-36 questionnaires) and selected health outcomes will be collected at 0, 1, 6 and 12 months after hospitalization for CAP.

The CHO-CAP study was approved by the Central Committee on Research involving Human Subjects in the Netherlands.

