**Data collected:**			
*Demographic data*	➣ Current living situation	➣ Current living situation	➣ Current living situation
*Quality-of-life data*			
➣ 5-item EQ-5D instrument & VAS [22]	➣ As on day of interview	As on day of interview	As on day of interview
	➣ Referring back to worst moment of CAP episode		
	➣ Referring back to time previous to CAP episode		
➣ 36-item SF-36D instrument [24,25]	n.a.^b^	➣ 36-item SF-36D instrument [24,25]	➣ 36-item SF-36D instrument[24,25]
*Co-morbidities*			
➣ Stroke and/or cardio-vascular event	➣ Since participating in CAPiTA;	➣ Since participating in CAPiTA,	➣ Since last contact moment;
➣ 28-item standard list of major comorbid diseases developed by Statistics Netherlands	➣ 28-item standard list of major comorbid diseases	➣ 28-item standard list of major comorbid diseases	n.a.^b^
*Medical resources used:*			
➣ Medication used	➣ Previous to hospital admission to treat CAP;	n.a.^b^	➣ Since last contact moment;
➣ GP; emergency department and other medical specialist consultations (phone; office and home consultation(s))	➣ Previous to hospital admission to treat CAP;	n.a.^b^	➣ Since last contact moment;
➣ Outpatient visit(s) and treatment(s)	n.a.^b^	n.a.^b^	➣ Since last contact moment;
➣ Hospital admission(s) and treatment(s)	n.a.^b^	n.a.^b^	➣ Since last contact moment;
➣ Institutional care admission(s) others than hospital	n.a.^b^	n.a.^b^	➣ Since last contact moment;
*Home care*			
➣ Professional home care used	➣ Previous to hospital admission during the CAP episode?	In month previous to interview	➣ Since last contact moment;
*Productivity losses due to absence from patient/control from unpaid work (including replacement)*			
➣ Is unpaid work conducted on a regular base.	➣ Previous to CAP hospital admission	n.a.^b^	➣ Since last contact moment;
➣ Absent from unpaid work: For how long. Who took the work over?	➣ Previous to hospital admission during the CAP episode?	n.a.^b^	➣ Since last contact moment;
*Productivity losses due to absence of caregiver(s) from (un)paid work*			
➣ Informal home care used: By who? And for how long?	➣ Previous to hospital admission during the CAP episode	n.a.^b^	Since last contact moment;
*Travel costs:*			
Method of transport and cost	➣ To hospital when admitted with CAP	n.a.^b^	n.a.^b^
	➣ After discharge from hospital to home/nursing home	n.a.^b^	n.a.^b^
*Other cost/out-of-pocket expenses* (open question)	n.a.^b^	n.a.^b^	➣ Since last contact moment;

Note:

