a) Questionnaires (in Dutch) are available on request from first author.

b) n.a. = not applied.

Similar procedures are followed for the controls. An identified and eligible control who expressed interest to participate at the time of vaccination is visited at home. If consent is given, a questionnaire similar to that administered in the “diseased” cohort is provided (see details in Table 2).

In both the “diseased” and “non-diseased” cohorts, further data is collected on 1, 6 and 12 months after the initial home visit. Questionnaires are send by post, with the request to fill-in and send back within a week. If no response is received, participants are contacted by phone. This follow-up questionnaire addresses current living conditions, quality-of-life, co-morbidities and healthcare resources used (Table 2). A new diary for recording of healthcare use and other out-of-pocket expenses in the forthcoming period is provided once the questionnaire has been returned.

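### At the baseline visit the SF-36 is given to controls only, contrary to the abstract, and professional home care is asked over windows that cannot be compared between the cohorts

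*Protocol article*

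**What the plan says.** The abstract (Methods/Design) gives one schedule for both quality-of-life instruments: "quality-of-life (using EQ-5D and SF-36 questionnaires) and selected health outcomes will be collected at 0, 1, 6 and 12 months after hospitalization for CAP". It also states the purpose of the matched comparison as estimating excess costs and quality-of-life changes attributable to CAP.

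Table 2 sets out the contacts by cohort. At the baseline home visit the SF-36 row is marked n.a. for the diseased cohort and lists the instrument for the non-diseased cohort. At 1, 6 and 12 months it applies to both. The table note defines the mark: "n.a. = not applied". EQ-5D and VAS are taken in both cohorts at the home visit ("As on day of interview").

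For professional home care at the same visit, patients are asked about use "Previous to hospital admission during the CAP episode", and controls about use "In month previous to interview". At the later contacts both cohorts report use since the previous contact. The text after Table 2 says that controls receive "a questionnaire similar to that administered in the" diseased cohort.

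The two primary objectives are between-cohort differences, over 12 months, in quality of life and in resource use. Matching is on age, gender and the EQ-5D score from vaccination.

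**The concern.** Two items at the same visit are not measured alike in the two cohorts, and the text gives no sign of it.

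For the SF-36, a reader of the abstract would expect four paired occasions and might plan a month-0 difference, a change score or an area under the curve from month 0. None of these can be formed for that instrument.

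For home care, the stake is the second primary objective. In people aged 65 and over, home care may well predate the pneumonia. Follow-up counts all use, whether or not it is linked to CAP. If patients already used more home care than their matched controls, that difference enters the excess attributed to CAP. A pre-index measure on a common window would allow adjustment, and Table 2 does not provide one. An analysis plan cannot recover data that were not collected.

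**Working it through.** **Stated counts.** The article's own figures reproduce: 84,496 × 0.30 = 25,349 (stated as about 25,000), 2,000 × 0.30 = 600 patients, and 600 × 2 = 1,200 controls. The point does not depend on them. It rests on setting the contact schedule side by side.

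**Step 1: quality-of-life occasions.** Month 0 is taken to be the home visit, from which the Data collection section counts the later contacts.

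| Instrument | Source | Patients | Controls | Common to both |
|---|---|---|---|---|
| SF-36 | Abstract | 0, 1, 6, 12 | 0, 1, 6, 12 | 0, 1, 6, 12 |
| SF-36 | Table 2 | 1, 6, 12 | 0, 1, 6, 12 | 1, 6, 12 |
| EQ-5D and VAS | Table 2 | 0, 1, 6, 12 | 0, 1, 6, 12 | 0, 1, 6, 12 |
| EQ-5D | Baseline cohort | vaccination | vaccination | vaccination |

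The two SF-36 lines differ in one cell: patients at month 0. Because the table note defines the mark as not applied, this is a design feature and not a cell lost from the table. Any SF-36 quantity that needs a month-0 value in both cohorts is therefore not estimable. EQ-5D changes from month 0 or from vaccination are estimable, and patients also give a recalled EQ-5D for the time before CAP.

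**Step 2: professional home care.**

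| Contact | Patients | Controls | Comparable? |
|---|---|---|---|
| Home visit | Before admission, within the CAP episode; no fixed length | One month before interview | No |
| 1, 6 and 12 months | Since previous contact | Since previous contact | Yes |

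The patients' window lies within the illness and varies in length. The controls' window is one month and has no illness in it. Even as a weekly rate the two answers describe different states.

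**Step 3: what this means for excess use.** Write D for the observed difference in home care over follow-up, E for the part caused by CAP, and B for the difference between patients and matched controls that would have existed without CAP. Then D = E + B. A pre-index measure in both cohorts would inform B. Table 2 supplies it for controls only.

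**Step 4: how far matching covers B.** Matching fixes age within 3 years, gender, and EQ-5D within 5 percentage points. The EQ-5D score dates from vaccination, which ran from October 2008 to 31 January 2010. Follow-up in the parent trial is event-driven (130 primary endpoints), so the interval from vaccination to CAP is not fixed. Care needs that arose in that interval are not matched, and prior home care is not a matching factor. Matching therefore reduces B but need not make it zero.

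**The case against.** The case on the other side is substantial.

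- **SF-36 at the visit would not be a pre-illness baseline.** Patients are visited after discharge, so an SF-36 taken then would already reflect the CAP episode, and change from it would measure recovery. Patients complete three EQ-5D assessments at that visit, so leaving out a 36-item form is defensible. This stands. It means that correcting the abstract is an acceptable remedy.
- **No month-0 SF-36 contrast is planned.** The abstract states data collection only. Neither the objectives nor the data analysis section names such a contrast, a change score or an area under the curve. This stands.
- **Matching and other data limit confounding in home care.** EQ-5D includes self-care and usual activities. Living situation and a 28-item comorbidity list are recorded in both cohorts at the home visit, and regression is foreseen. This stands in part: none of these measures prior use of care.
- **The question to patients may capture continuing care, and the full questionnaires are not shown.** This is possible, but as tabulated the window is the illness episode, which does not give a usual level.
- **Items on treatment of CAP before admission have no counterpart in controls.** This stands. Asking them of patients only is ordinary episode costing.

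A reader might also infer that no change-from-baseline comparison is possible, or that the primary objectives fail. The documents do not support either: EQ-5D is available in both cohorts at vaccination and, with VAS, at the home visit, and home-care use at follow-up is asked over the same windows in both.

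**Conclusion.** The point holds in a limited form. The abstract and Table 2 disagree on the SF-36 at month 0. One of the four collection occasions lacks a value in the whole diseased cohort, so an SF-36 difference at month 0 and an SF-36 change from month 0 cannot be compared between cohorts. SF-36 differences at 1, 6 and 12 months remain valid, as do the EQ-5D comparisons.

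Separately, baseline professional home care has no like-for-like value across cohorts, so pre-existing need cannot be distinguished from CAP-attributable use beyond what matching and comorbidity adjustment achieve. A reader might want this expressed in hours of overstated care. The documents give no pre-index home-care figure, so any such number would be an assumed weekly gap multiplied by 52 weeks and would not measure bias. The direction is also not established.

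The conclusion assumes that Table 2 describes the questionnaires accurately. Both primary objectives can still be addressed. The changes are worth making because they are cheap, and the home-care change would reduce confounding in the second objective.

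**What to change.** 1. **SF-36.** Choose one course. (a) Give it to both cohorts at the home visit, and state that in patients it is an early post-discharge value and not a pre-CAP baseline. (b) Correct the abstract to show month-0 SF-36 in controls only, limit between-cohort SF-36 comparisons to 1, 6 and 12 months, and base change from baseline on EQ-5D.
2. **Home care.** Keep the CAP-episode question for episode costing. Add, for patients, a question on home care in the month before CAP onset, to match the one-month question already put to controls. Use it as a covariate in the home-care and cost models. If it is not collected, keep baseline home care out of the between-cohort contrast.

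The visit already takes place in both cohorts. The cost is a few minutes of respondent time (one 36-item form under option 1a, wording only under 1b) and some recall error about the month before CAP.

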**Discussion:**

With an expected 600 CAP episodes this study will be one of the biggest prospectively studied cohorts of hospitalized elderly with CAP with regard to resources use and Qol data. Strengths of this study further include collection of out-of-pocket costs of patients and productivity losses of both patients and their caregivers and the follow-up period of up to one year post-discharge. This study is therefore expected to add more in-depth knowledge on the short and longer term outcomes of pneumonia in elderly.

**Trial registration:**

ClinicalTrials.gov, NCT00812084.

## Background

The Community Acquired Pneumonia Immunization Trial in Adults (CAPiTA) is a randomized placebo-controlled double-blind trial to determine the efficacy of a 13-Valent Pneumococcal Conjugate Vaccine (13vPnC) in the prevention of vaccine-serotype pneumococcal community-acquired pneumonia (CAP) and invasive pneumococcal disease (IPD) [1]. Within the CAPiTA trial, 84,496 volunteers aged 65 and over, dispersed over the Netherlands, received 13vPnC or placebo in a single-dose vaccine between October 2008 and 31 January 2010. Objectives with regard to efficacy, safety and health outcomes have been described elsewhere [1]. In case of clinical vaccine effectiveness for CAP prevention, drug-licensing and governmental bodies will require detailed information on the cost-effectiveness of this vaccine in elderly in order to decide whether restricted (financial) resources have to be invested in widespread use of this vaccine [2,3]. If clinically effective, this vaccine might reduce healthcare resource use, increase quality-of-life and reduce mortality in elderly. These effects stretch beyond the hospitalization period, as covered in the CAPiTA trial.

There are few recent cost estimates for CAP, and none of them have been derived from Dutch patients [4]. The few prospectively conducted studies (e.g. [5-8]) considered only direct healthcare costs during hospitalisation, had no or limited follow-up post-discharge, and most had a relative small sample size [7,8]. Larger cost studies were mainly retrospective, focussing mostly on direct healthcare costs of patients hospitalised with CAP, with no or limited follow-up post-discharge [4,7,9-18]. However, since CAP may influence the occurrence of other disease events (i.e. stroke and other cardiovascular events [19,20]) in the post-discharge period, it is important to include all healthcare resource use, not only resource use related to the index CAP episode. Also, post-discharge mortality is non-negligible in this population [21]. It is therefore important to have a follow-up period that is much longer than the immediate CAP-related hospitalization period when estimating costs associated with CAP.

The “Costs, Health status and Outcomes of CAP” study (CHO-CAP), in full “Collecting health outcomes and economic data on hospitalized Community-Acquired Pneumonia – a prospective cohort study”, is designed to prospectively determine health outcomes, quality-of-life (QoL) and costs associated with CAP for a period of 12 months after hospitalization due to CAP.

### Objective

CHO-CAP comprises the collection of cost data and quality-of-life data in elderly with and without CAP. The primary objectives are:

1. To determine, during a 12 month follow-up period, differences in quality-of-life of elderly with and without CAP.

2. To determine, during a 12 month follow-up period, differences in resource use (healthcare and non-healthcare) in elderly with and without CAP.

The secondary objective is to describe the baseline health status and quality-of-life of a community-dwelling elderly population eligible for participation in the CAPiTA study.

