#### Nested matched cohort study

As part of the CAPiTA trial, patients with a clinical suspicion of CAP are tracked in 56 Dutch sentinel hospitals. The duration of follow-up within CAPiTA is defined by the number of primary endpoints captured (i.e. 130 first CAP episodes caused by vaccine-type *S. pneumoniae* serotypes). It is expected that around 2,000 CAP episodes will occur within the study population [1]. Assuming a response rate of ~30%^a^ for the baseline questionnaire, we expected approximately 600 first CAP episodes among CHO-CAP participants. Local research nurses in sentinel hospitals notify the CHO-CAP team of newly admitted CAPiTA patients with a clinical suspicion of CAP directly after hospital admission and at the time of discharge. After discharge, eligible patients (i.e. CHO-CAP participants) will be asked to participate in the prospective cohort study for a period of one year. Patients are informed (orally and by written information) that participation involves one interview during a home visit, with three subsequent questionnaires to be completed during the 12 month period. Patients again provide informed consent upon inclusion in the prospective cohort study. Exclusion criteria for the prospective cohort study are hospitalization for a second (or further) hospitalization for CAP related complaints, inability to complete questionnaires, or a recent diagnosis of malignancy as the study was considered too burdensome for this latter group.

For each patient with CAP in the prospective cohort study (“diseased” cohort), two matched unaffected subjects (i.e. no CAP episode until the time of matching) will be selected from the baseline population for inclusion in the “non-diseased” cohort (see Figure 1). Matching is based on age (same age, with allowance of 3 years age difference), gender and baseline health status (same EQ-5D score [22], with maximum allowance of 5 percent points difference). Expectations are that both in the short-term and the medium term, CAP patients consume more medical resources, require more (in)formal help, might experience more trouble to get back to their daily activities, and have a lower quality-of-life than their non-diseased peers. Furthermore, mortality, both within-hospital as during the 12 months follow-up period, is expected to be higher in CAP patients than in controls.

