**Anxiety/depression**	
I am not anxious or depressed	□
I am moderately anxious or depressed	□
I am extremely anxious or depressed	□

After receipt of the completed baseline questionnaire, CAPiTA participant ID, informed consent, socio-demographic data, and EQ-5D index value for health status (see below) were registered in the CHO-CAP database, with linkage to the CAPiTA database for age, gender and place of residence/region. Regular updates to adjust for changes in place of residence or to include loss-to-follow up (e.g., due to death), take place.

Following the standards set up by the Euroqol organisation, the developers and owners of the EQ-5D instrument [22], the 5-items from the EQ-5D questionnaire were transferred into a single value between 0 (worst imaginable health status) and 1 (best imaginable health status) [23].

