## Discussion

The infrastructure of the CAPiTA trial offers a unique opportunity for prospective collection of health outcomes, QoL and cost data of patients hospitalized with CAP. Such data will facilitate the construction and validation of health economic models on cost-effectiveness and cost-utility of 13vPnC in the future, should this become necessary if vaccine efficacy and safety is demonstrated.

One of the limitations of the current study is that we might mainly reach the ‘healthier’ part of the community-dwelling CAPiTA participants, as older and more diseased subjects may be less willing to participate in additional research projects next to the main CAPITA trial. To gain insight into this possible bias, we will compare the baseline demographic data of the CHO-CAP cohort population with the larger CAPiTA population. Further, data gathered within the CAPiTA-study will enable us to compare CAP cases from the current CHO-CAP cohort with all CAP cases, for instance with regard to duration of hospitalization and occurrence of complications.

With an expected 600 CAP episodes we expect to constitute one of the biggest prospectively studied cohorts of hospitalized elderly with CAP with regard to resources use and QoL data. Strengths of this study further include collection of out-of-pocket costs of patients and productivity losses of both patients and their caregivers and the follow-up period of up to one year post-discharge. Our study is expected to add more in-depth knowledge on the short and longer term outcomes of pneumonia in elderly.

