## Endnote

^a^Commercial marketing questionnaires without any involvement of the participants normally reach a response rate around 20%. Healthcare questionnaires are known to obtain slightly higher response rates, whereby the greater the involvement, the higher the response rate. Given their previous participation in the CAPiTA study we expected some involvement from these participants for the current study, and therefore a response rate of 30% was expected to be feasible.

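### The secondary objective names the population eligible for CAPiTA, but the baseline cohort is a self-selected group, expected at about 30%, of people already vaccinated, and the overall EQ-5D is planned as observed

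*Protocol article*

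**What the plan says.** - **Target.** The Objective section sets the secondary objective as to "describe the baseline health status and quality-of-life of a community-dwelling elderly population eligible for participation in the CAPiTA study".
- **Source.** The Background gives the parent trial population: "84,496 volunteers aged 65 and over, dispersed over the Netherlands, received 13vPnC or placebo in a single-dose vaccine".
- **Who enters the baseline cohort.** The Baseline cohort section says CHO-CAP information was handed out after CAPiTA inclusion and vaccination. Those who returned a questionnaire with signed consent form the cohort.
- **Expected response.** The Nested matched cohort section under Study design reads: "Assuming a response rate of ~30%^a^ for the baseline questionnaire, we expected approximately 600 first CAP episodes among CHO-CAP participants". The Endnote presents this as a planning judgement: "therefore a response rate of 30% was expected to be feasible". The Abstract puts the cohort at about 25,000.
- **Planned presentation.** Descriptive statistics presents health status as observed, with and without stratification for age, gender and/or baseline EQ-5D, as mean, median and percentiles. Statistical analysis adds a comparison of health status across age groups in the baseline population.
- **Acknowledged selection.** The Discussion expects to reach mainly the healthier CAPiTA participants, "as older and more diseased subjects may be less willing to participate in additional research projects". Its response is: "we will compare the baseline demographic data of the CHO-CAP cohort population with the larger CAPiTA population".
- **Data at hand.** The Data collection section on the baseline cohort says records were registered "with linkage to the CAPiTA database for age, gender and place of residence/region".

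**The concern.** Two selection steps separate the population in the objective from the people measured. The first runs from eligible to enrolled and vaccinated, and the article describes nothing that informs it. The second runs from vaccinated to questionnaire responder, and about 70% are expected to drop out there. The article expects that loss to depend on age and health, and health is what this objective measures.

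The demographic comparison would reveal an imbalance in age or gender but would not change the EQ-5D results. Stratified tables help within age and gender groups. The single overall mean and the overall percentiles still reflect whatever age and gender mix happened to respond. Stratifying by baseline EQ-5D cannot address selection on EQ-5D itself.

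At stake is how the headline baseline figure is read. Under the objective's wording it could be taken as a value for eligible community-dwelling elderly people, when it describes a probably healthier subgroup. A large number of responders reduces sampling error but not this kind of error.

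**Working it through.** **1. Reproduce the plan's own figure.** 84,496 x 0.30 = 25,349, which agrees with the stated figure of about 25,000. Also 2,000 x 0.30 = 600, the expected number of CAP episodes among CHO-CAP participants.

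**2. Inputs.**
- From the article: N = 84,496; response rate r = 0.30 (an expectation, not an achieved rate); n about 25,000.
- Assumed, because the article gives neither: SD of the EQ-5D index, 0.15 to 0.25; gap d = responder mean minus non-responder mean, varied from zero upwards.

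**3. Where the bias comes from.** Taking CAPiTA participants as the target, the bias of the unweighted responder mean is

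bias = (1 - r) x d = 0.70 x d.

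With strata h of age, gender and region, let p_h be the responder share, P_h the CAPiTA share, r_h the response rate, and m_h and u_h the responder and non-responder means. The same bias splits into two parts:

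bias = sum of (p_h - P_h) x m_h + sum of P_h x (1 - r_h) x (m_h - u_h).

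The first part is the mix of responders, and standardisation removes it. The second is health-related nonresponse within strata, and standardisation leaves it untouched. The article gives no stratum-specific rates or means, so neither part can be computed.

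**4. Scale of sampling error (illustration).** 95% half-width = 1.96 x SD / sqrt(25,000). The gap at which bias equals the half-width is half-width / 0.70.

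| Assumed SD | Half-width | Gap at which bias equals half-width |
|---|---|---|
| 0.15 | 0.0019 | 0.0027 |
| 0.20 | 0.0025 | 0.0035 |
| 0.25 | 0.0031 | 0.0044 |

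**5. Bias over a range of gaps, SD 0.20.**

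| Assumed gap d | Bias 0.70 x d | Bias in half-widths |
|---|---|---|
| 0 | 0 | 0 |
| 0.002 | 0.0014 | 0.6 |
| 0.005 | 0.0035 | 1.4 |
| 0.01 | 0.007 | 2.8 |
| 0.02 | 0.014 | 5.6 |
| 0.05 | 0.035 | 14 |

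These figures cover only the second selection step. Nothing in the article allows a calculation for the step from eligible to enrolled.

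**The case against.** The strongest case on the other side has five parts.

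- **The limitation is disclosed.** The Discussion gives its direction and reason and plans a check. This stands, but disclosure does not alter the reported estimate or the objective's wording.
- **Stratified results are already planned.** Age- and gender-specific figures expose two of the three imbalances, and a reader holding the CAPiTA age and gender distribution could standardise a mean from them. This largely stands, and it limits the point to the overall figures. It does not help with region.
- **Weighting may be specified elsewhere.** The article condenses a fuller protocol, and an analysis plan may exist. This also stands: the absence of a weighting method would not be a finding by itself. The mismatch between the objective's population and the cohort is in the text shown, as is the statement that health status is presented as observed.
- **The article does not say the results will be offered as population values.** Descriptive statistics refers to the baseline cohort. That is fair, but the Objective names the wider population, so the two sections need to agree.
- **Weighting corrects only part of the problem.** True. Sicker people of the same age, gender and region may still respond less.

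A reader might go further and infer that the bias is bound to far exceed the plan's precision, for instance by 11 to 28 standard errors (0.014 / 0.00126 and 0.035 / 0.00126). The documents do not support this. They state no precision for this objective. Those multiples rest wholly on an assumed gap of 0.02 to 0.05 and an assumed SD of 0.20, and they count the whole gap rather than the part that weighting could remove.

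**Conclusion.** The point holds in a limited form. The objective's population is broader than the group sampled, and the safeguards described diagnose or stratify without correcting the overall EQ-5D mean and percentiles.

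The size of the bias is unknown. Conditional on n about 25,000, a 30% response and an SD of 0.15 to 0.25, a responder/non-responder gap above roughly 0.003 to 0.004 would push the bias beyond the 95% half-width. A smaller gap would leave it within sampling error, and a zero gap would give none. So a large sample gives little reassurance here, but a large bias has not been shown.

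The consequence is confined to a secondary, descriptive objective. Nothing in this point affects the two primary objectives, which rest on the matched comparison of CAP patients with controls. The change is worth making because it is cheap and alters both the overall result and what it can be said to represent.

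**What to change.** 1. Restate the population in the secondary objective as questionnaire responders among CAPiTA participants. If the standardised figures below become the main presentation, CAPiTA participants would be acceptable. In neither case should it be everyone eligible for the trial.
2. Present the overall baseline EQ-5D mean and percentiles standardised to the 84,496 CAPiTA participants by age group, gender and region, next to the unweighted and stratified figures already planned. Post-stratification or inverse-probability-of-response weights would both serve.
3. State beside the result that health-related nonresponse within those strata remains, and that the step from eligible to enrolled is not addressed.

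The cost is a few lines of analysis on variables already linked for responders, plus the distribution in the full trial population, which the planned demographic comparison largely needs anyway. The downsides are a small loss of precision from weighting, of little weight with about 25,000 responders, and incomplete removal of bias.
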